### Study design

This is a mixed (retrospective and prospective) longitudinal observational study designed to evaluate the association between chronic use of amiodarone (AMIO) and the following:

(I)**Primary outcome:** inflammatory profile, serologic reactivity to anti-*T. cruzi* antibody, and parasitic load;(II)**Secondary outcomes:** cardiovascular events (new sustained atrial arrhythmias, new sustained or non-sustained ventricular tachyarrhythmias, stroke, heart failure, atrioventricular block, and cardiovascular hospital admissions), CCC progression, internal cardioverter-defibrillator (ICD) implantation, heart transplantation, all-cause death, and a composite endpoint (including the aforementioned cardiovascular events, disease progression, ICD implantation, heart transplantation, and death).

Patients with CCC who take AMIO (exposed group) will be compared with those who do not take this drug (non-exposed group). To minimize potential confounding, patients will be matched based on the stage of CCC according to the Brazilian Consensus on Chagas Disease (A and B1 *versus* B2 and C), age (<50 years *versus* >50 years), and sex (female *versus* male) [15].

Clinical and laboratory data including blood tests, ECG, transthoracic two-dimensional echocardiography (ECHO), and 24-hour Holter monitoring, will be evaluated at three different time points:

(i)**Retrospective data**: from up to 3 years before the start of the study;(ii)**Baseline/recruitment**: at the time of inclusion in the study;(iii)**Prospective data**: during the 2 years of follow-up after recruitment;

The duration of the study, totaling five years of clinical follow-up, was established considering the CCC progresses at a rate of approximately 2% per year [22]. At recruitment, blood samples will be collected for biochemical and molecular analyses to obtain information related to the study’s primary outcome (Table 1) (Fig 1).

**Table 1 pone.0347305.t001:** AMIO-CHAGAS’s study Chronogram: Enrollment, Interventions and Outcome Assessments.

			Retrospective data	Recruitment	Prospective data
			2020 −2022	2023 - 2025	2025 - 2027
**Primary outcome:**	**Immunomodulatory effect**	Gene expression of CCC progression biomarkers in PBMCs	**–**	**x**	**–**
		Determination of serum levels of cytokines and nitric oxide	**–**	**x**	**–**
	**Trypanocidal effect**	Determination of anti-*T. cruzi* antibody titers	**–**	**x**	**–**
		*T. cruzi*-antigen quantification	**–**	**x**	**–**

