### Study population

Participant recruitment began on March 7, 2023, and is expected to be completed by December 2025. Participants are being recruited sequentially during their routine medical visits. Patients using AMIO are identified from the database of individuals monitored by the Clinical Research Laboratory on Chagas Disease at INI-Fiocruz. Only patients who have been receiving AMIO for at least three months will be included, ensuring adequate tissue impregnation with a cumulative dose of 10 g [23].

Inclusion criteria are as follows:

Confirmed diagnosis of CD, based on two serological tests with different methodologies (enzyme-linked immunosorbent assay [ELISA] and chemiluminescence) [14,15];Individuals over 18 years of age;Patients classified within the following CCC stages: A, B1, B2, and C [15].

Exclusion criteria are as follows:

Co-infection (HIV, hepatitis B and C, HTLV, Hansen’s disease, leishmaniasis and paracoccidioidomycosis);Immunosuppression of any nature;Cancer;Patients with stage D of CCC will be excluded due to their complex clinical management, including frequent hospitalizations and medication adjustments, which could affect the study’s feasibility.

Patients meeting the inclusion criteria will be invited to participate in the study, and written informed consent will be obtained from all individuals who agree to enroll.

Importantly, AMIO use was prescribed at medical discretion to treat atrial or ventricular arrhythmias [12], independently of this study, characterizing an observational study design.

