### Statistical analysis

Descriptive statistics were used to summarize the characteristics of the study population. Continuous variables will be presented as medians and interquartile ranges (IQR), and categorical variables as absolute and relative frequencies. Missing data will be assessed for their pattern and mechanism (i.e., missing completely at random (MCAR), missing at random (MAR), or missing not at random (MNAR)). The primary approach to handling missing data will be determined once the dataset is available. Depending on the extent and nature of missingness, appropriate strategies may include multiple imputation, complete case analysis, or sensitivity analyses to evaluate the robustness of the findings. The Shapiro-Wilk test will be used to assess the normality of continuous variables. When distributions deviate from normality, appropriate transformations or non-parametric tests will be applied.

Comparisons of patient characteristics according to AMIO use will be evaluated using the independent Student’s t-test for normally distributed continuous variables or the Mann-Whitney U-test for non-normally distributed data. Categorical variables will be compared using the chi-square test or Fisher’s exact test, as appropriate. Correlations between continuous variables related to the primary outcome will be assessed using Pearson or Spearman correlation coefficients, depending on data distribution. AMIO use and longitudinal changes in continuous variables will be analyzed using mixed linear models, adjusted for the duration of amiodarone use. Analyses of time course outcomes (e.g., cardiovascular events, disease progression, all-cause mortality) will be conducted using Cox proportional hazards regression models adjusted for potential confounders such as age, sex, comorbidities and previous etiologic treatment. Hazard ratios (HRs) and their 95% confidence intervals (CI) will be reported. A two-sided p-value ≤ 0.05 will be considered statistically significant.

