## Discussion

Although no clinical studies have specifically investigated the impact of AMIO treatment on mortality reduction in patients with CCC, some research suggests a beneficial effect of this drug on the survival rates of patients with ventricular arrhythmias of other etiologies. In the 1990s, the Argentine GESICA study (Randomized Trial of Low-dose Amiodarone in Severe Congestive Heart Failure), and the North American CHF-STAT study (Congestive Heart Failure: Survival Trial of Antiarrhythmic Therapy) evaluated whether the treatment with AMIO in patients with congestive heart failure affected survival [32,33]. The GESICA trial reported that AMIO was effective in reducing mortality in individuals with congestive heart failure (CHF) [32]. In contrast, the CHF-STAT trial showed that although AMIO suppressed arrhythmias and improve ventricular function, it did not reduce the incidence of sudden death or improved overall survival [33].

The main reason suggested for these discrepant results was the differing proportions of patients with ischemic versus non-ischemic heart disease: 39% and 61% in GESICA compared to 71% and 29% in CHF-STAT, respectively. Furthermore, nearly 10% of the patients in the GESICA trial had CCC, whereas this condition was absent in CHF-STAT. These differences raise the possibility that AMIO may have a greater impact on reducing mortality in individuals with CCC [34].

Additionally, the BENEFIT study (2015) evaluated the effect of BZN in chronic patients with CCC and concluded that, although the treatment reduced the detection of *T. cruzi* in the blood, it did not reverse or prevent the progression of Chagas heart disease. Notably, the subgroup of patients receiving a combination of AMIO and BZN was the only one to show a reduction in hospitalizations and risk of cardiovascular death [35]. This clinical observation from a randomized clinical trial was further supported by animal model studies. In a mouse model of CD, the BZN/AMIO combination was more effective in reducing inflammation and cardiac fibrosis than either monotherapy [36,37]. These complementary preclinical and clinical findings strengthen the rationale and provide robust support for our hypothesis that AMIO may exert immunomodulatory and trypanocidal effects in humans with CCC, which is the focus of the present study.

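### The plan states control for previous etiologic treatment only in its Cox models, not in the amiodarone comparison of parasite load and anti-T. cruzi reactivity, which are primary outcomes

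*Protocol article*

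**What the plan says.** **Eligibility (Study population).** The inclusion list asks for confirmed disease, adult age and a stage: "Patients classified within the following CCC stages: A, B1, B2, and C". The exclusion list is co-infection, "Immunosuppression of any nature", cancer and stage D. Neither list mentions etiologic treatment.

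**Matching (Study design).** The article says "patients will be matched based on the stage of CCC according to the Brazilian Consensus on Chagas Disease", together with age and sex. Treatment history is not a factor.

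**Outcome and timing (Study design, Table 1).** The primary outcome is introduced as "inflammatory profile, serologic reactivity to anti" T. cruzi antibody, plus parasitic load. Table 1 groups antibody titres and T. cruzi quantification as the trypanocidal effect and marks them at recruitment only. The text agrees: "At recruitment, blood samples will be collected for biochemical and molecular analyses".

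**Adjustment (Statistical analysis).** The Cox models are "adjusted for potential confounders such as age, sex, comorbidities and previous etiologic treatment". Longitudinal changes in continuous variables are to be analysed with "mixed linear models, adjusted for the duration of amiodarone use". Comparisons by amiodarone use are otherwise t-test or Mann-Whitney, without covariates.

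**Background knowledge (Discussion).** The article reports that benznidazole lowered detection of T. cruzi in blood in a randomised trial of chronic cardiomyopathy.

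**The concern.** The plan names previous etiologic treatment as a confounder and controls for it where the link is indirect (clinical events). It states no control where its own Discussion makes the link direct (parasite in blood).

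Amiodarone was prescribed at the physician's discretion, so nothing in the design balances treatment history between users and non-users, except as far as history happens to follow stage, age or sex. With a single sample and none from before amiodarone, a within-patient comparison cannot correct an imbalance afterwards.

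At stake is the trypanocidal half of the primary outcome. If more users than non-users had earlier benznidazole, amiodarone could appear to lower parasite load when it does not. If fewer had it, a real effect could be hidden.

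**Working it through.** The plan gives no figure on this point: no treated shares and no size for the benznidazole effect. The check first sets the sections side by side and then shows what an imbalance would do under stated assumptions.

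**1. Does any stated step control for treatment history on these endpoints?**

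| Step | Covers treatment history? | Applies to parasite load and serology? |
|---|---|---|
| Inclusion and exclusion criteria | No | Yes |
| Matching on stage, age, sex | No | Yes |
| t-test or Mann-Whitney by amiodarone use | No | The only two-group test given for continuous data |
| Mixed model, amiodarone duration as covariate | No | Written for longitudinal change; these are measured once |
| Cox model | Yes | No, time-to-event outcomes only |

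The one step that uses treatment history does not apply to these endpoints.

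**2. Illustration with PCR positivity.** Assumed: 50% positive if never treated, 20% if treated, no amiodarone effect. For a treated share s, positivity = (1 − s) × 50% + s × 20%.

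- 40% treated among users: 0.6 × 50% + 0.4 × 20% = 38%. 20% among non-users: 0.8 × 50% + 0.2 × 20% = 44%. Spurious difference: 6 points.
- 60% against 10%: 0.4 × 50% + 0.6 × 20% = 32%, and 0.9 × 50% + 0.1 × 20% = 47%. Spurious difference: 15 points. This split is extreme.
- Equal shares: difference 0. Reversed shares: same size, opposite sign.

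For 38% against 44% with 45 per group (Sample size section), the standard error is √[(0.38 × 0.62 + 0.44 × 0.56)/45] = √(0.482/45) = 0.1035. Then 0.06/0.1035 = 0.58, and the two-sided 5% test rejects with probability P(Z > 1.38) + P(Z < −2.54) ≈ 0.09.

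**3. Illustration on a continuous scale.** Assumed: earlier benznidazole shifts the marker by g within-stratum SDs; shares pA (users) and pU (non-users); no amiodarone effect.

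- Bias = g × (pA − pU)
- Variance of the difference = {[1 + g²pA(1 − pA)] + [1 + g²pU(1 − pU)]}/45

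Example, g = 1, 40% against 20%: bias 0.20; variance (1.24 + 1.16)/45 = 0.0533; standard error 0.231; ratio 0.87; rejection 13.9%.

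| Treated, users v non-users | g = 0.5: bias, rejection | g = 1.0 | g = 1.5 |
|---|---|---|---|
| 20% v 20% | 0; 5.0% | 0; 5.0% | 0; 5.0% |
| 30% v 20% | 0.05; 5.6% | 0.10; 7.2% | 0.15; 9.2% |
| 40% v 20% | 0.10; 7.5% | 0.20; 13.9% | 0.30; 21.9% |
| 50% v 20% | 0.15; 10.7% | 0.30; 25.4% | 0.45; 42.3% |

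With 20% against 40% the bias changes sign and the rejection rate equals that of 40% against 20%.

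**4. What stratifying does.** In step 2, within the never-treated the comparison is 50% against 50%, and within the treated 20% against 20%. The spurious difference disappears in each stratum, whatever the shares.

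**The case against.** **It is a matter for the SAP.** The article is condensed, its confounder list is open-ended, and its t-test sentence speaks of patient characteristics. An unseen SAP may well adjust the primary outcomes. This stands in part: the article does not rule out such adjustment. But it does state adjustment sets, puts this confounder in one and leaves it out of the other, and eligibility and matching are design features that it fixes itself.

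**Confounding needs an imbalance, and none is shown.** This stands. With equal shares the bias is zero. The point is that nothing stated secures equal shares.

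**The antibody half is not documented.** This also stands. The Discussion speaks of detecting the parasite in blood; no section says benznidazole lowers antibody reactivity. Serology belongs in the fix because the plan reads both measures as one trypanocidal effect and the same covariate costs nothing more.

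A reader might infer three stronger points that the document does not support:

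- *That patients on benznidazole at the blood draw are enrolled without washout.* The article is silent; the only treatment it names is previous treatment.
- *That amiodarone and benznidazole interact on the trypanocidal endpoints, so that a covariate could not suffice.* The statement that "the subgroup of patients receiving a combination of AMIO and BZN was the only one to show a reduction in hospitalizations" concerns hospitalizations and, as it continues, cardiovascular death; the mouse data concern inflammation and fibrosis. Neither concerns parasite load or serology.
- *That a lower load or titre can never be attributed to amiodarone because of this.* The problem depends on an unknown imbalance and can be repaired in the analysis. The study also calls itself exploratory and states its aim as an association.

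**Conclusion.** The point holds in limited form. Previously treated patients are eligible, treatment history is not a matching factor, and the stated adjustment for it serves only the Cox models. Parasite load, a primary outcome sampled once, is affected by benznidazole on the article's own account. Followed as written, the plan leaves a confounder that it names itself without stated control in the trypanocidal comparison.

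The size cannot be derived from the document. Over the assumed range (benznidazole effect 0.5 to 1.5 SD, treated shares 40–50% against 20%, 45 per group, no amiodarone effect), false-positive rates run from about 7.5% to 42%. The milder PCR scenario gives about 9%, and equal shares give 5%. The direction is open. For antibody reactivity, the bias rests on the further assumption that benznidazole changes it.

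**What to change.** In the Statistical analysis section, state that the amiodarone comparison of parasite load and anti-T. cruzi reactivity will be adjusted for, or stratified by, previous etiologic treatment (ever/never), using the history already needed for the Cox models. Add a comparison in never-treated patients as a sensitivity analysis.

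The cost is one more model term and a smaller sample in the sensitivity analysis: if 30% were treated (an assumption), 0.7 × 45 leaves about 31 per group, and some matches may be broken.

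Restricting the primary comparison to never-treated patients is not needed to deal with this confounder and would bring that loss into the main analysis. A fourth matching factor is not worth adding either: recruitment was due to end by December 2025, so it would reach few patients and would mix two matching schemes. Eligibility and patient care need no change.

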### Blood collection and isolation of plasma, serum and peripheral blood mononuclear cells (PBMCs)

Venous blood will be collected by hospital staff during the routine consultation of patients enrolled in the study. Two samples of 5 mL each will be collected: one in BD Vacutainer® Plus Plastic Serum tubes and kept for at least 30 minutes at room temperature to obtain serum, and one in BD Vacutainer® Plus Plastic EDTA K3 tubes (Becton, Dickinson, New Jersey, USA), for the separation of PBMCs and plasma by Histopaque 1077 gradient (Sigma Aldrich™, St. Louis, USA) following the manufacturer’s protocol (GE Healthcare). At the end of the separation procedure, the cells will be resuspended in 100 μL of TRI reagent (Sigma-Aldrich) and stored at −80º C until further analysis, such as plasma and serum. Biological samples will be stored during the study in accordance with established technical, ethical, and operational regulations, under institutional responsibility and the supervision of the principal investigator. Samples will be stored for up to five years after study completion and then discarded according to institutional biosafety regulations. During this period, samples may be used in additional subprojects subject to appropriate ethical approval.

### Analysis of gene expression of CCC progression biomarkers in PBMCs

The assessment of gene expression for key inflammatory and regulatory markers, including TNF, IFN-ɣ, IL-10, TGF-β, iNOS, and NF-κβ, in PBMCs provides valuable insights for monitoring systemic immune responses associated with chronic Chagasic cardiomyopathy (CCC) progression [24,25]. For this purpose, RNA will be extracted from collected PBMCs using TRI reagent (Sigma-Aldrich). cDNA synthesis will be performed with the SuperScript III First-Strand Synthesis kit (Thermo Fisher Scientific, Waltham, MA, USA), according to the manufacturer’s specifications. Gene expression will be measured by real-time quantitative PCR (RT-qPCR), using the following TaqMan gene expression assays: TNF (tumor necrosis factor; Assay ID: Hs00174128_m1), IFN-ɣ (interferon-gamma; Assay ID: Hs03044218_g1), IL-10 (interleukin; Assay ID: Hs00961622_m1), TGF-β (transforming growth factor beta; Assay ID: Hs00998133_m1), iNOS (inducible nitric oxide synthase; Assay ID: Hs01075529_m1) and NF-κβ (nuclear factor kappa β; Assay ID: Hs00765730_m1). Experiments will be conducted on a QuantiStudio 7 Pro Real-Time PCR System (Applied Biosystems), according to the manufacturer’s instructions. Gene expression will be calculated by relative quantification, using the Expression Suite software (V1.3), on the Molecular Analysis Platform RTP09J (FIOCRUZ/RJ).

### Determination of serum levels of cytokines and nitric oxide

In addition to gene expression analysis of inflammatory markers in PBMCs, quantification of cytokine levels and nitric oxide in the serum of patients with chronic Chagasic cardiomyopathy (CCC) has previously been associated with the progression of symptomatic forms of the disease [26]. Accordingly, detection of IL-2, IL-17, IL-4, IL-6, IL-10, TNF, and IFN-ɣ will be performed using the Cytometric Bead Array Human Th1/Th2/Th17 kit (Becton Dickinson), following the manufacturer’s protocol. Furthermore, nitrate and nitrite concentrations will be quantified in patient serum samples using the Griess reaction (Sigma-Aldrich), according to the manufacturer’s specifications.

### Determination of anti-*T*. *cruzi* antibody titers and antigen quantification

Previous studies have indicated that reduced serological reactivity and lower anti-*T. cruzi* antibody titers may be associated with improved prognosis in CCC, as these changes have been correlated with improvements in patients’ electrocardiographic profiles [27,28]. Based on this evidence, in the present study, the serological reactivity of anti-*T. cruzi* antibodies will be determined using the commercial Chagastest-Wienner kit (ELISA recombinant v.4.0), following the manufacturer’s recommendations. Positive and negative controls will be included to ensure test functionality. The cut-off value will be calculated as the mean absorbance of the negative controls, with the indeterminate zone defined as within ±10% of the cut-off value. In parallel, antigen quantification will be performed to enable subsequent correlation between these two parameters. For the detection and quantification of *T. cruzi* in patient samples, the NAT Chagas kit (Nucleic Acid Test for Chagas Disease) (IBMP, Curitiba, Brazil) will be used. This kit, based on a duplex TaqMan assay targeting the nuclear satellite DNA of *T. cruzi* and an exogenous internal amplification control, offers a quantification range from 10⁴ to 0.5 parasite equivalents per milliliter of blood. The assays will be performed according to the manufacturer’s instructions.

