**Continuous variables included:**

(i)Gene expression levels of TNF, IFN-γ, IL-10, TGF-β, iNOS, and NF-κB in PBMCs, quantified by RT-qPCR and expressed as fold change (arbitrary units);(ii)Serum cytokine concentrations—including IL-2, IL-4, IL-6, IL-10, IL-17, TNF, and IFN-γ—quantified in pg/mL using a Cytometric Bead Array (CBA);(iii)Serum levels of nitrate and nitrite (μM), determined by the Griess reaction;(iv)Anti-*Trypanosoma cruzi* IgG antibody titers, quantified by ELISA and reported as absorbance values;(v)Parasitic DNA load (parasite equivalents/mL), quantified by duplex TaqMan qPCR using the NAT Chagas kit;(vi)Left ventricular systolic ejection fraction (LVEF, %), as well as left ventricular diastolic and systolic volumes (mL), quantified using Simpson’s biplane method of discs via two-dimensional transthoracic echocardiography;(vii)Left ventricular diastolic function (graded by established echocardiographic criteria), right ventricular (RV) systolic function (expressed as fractional area change or TAPSE in mm), and strain parameters (%) of the left atrium (LA), right ventricle (RV), and left ventricle (LV), evaluated to provide a comprehensive assessment of cardiac mechanics;(viii)Electrocardiographic parameters: heart rate (beats per minute, BPM) and electrocardiographic intervals, including PR interval (ms), QRS duration (ms), QT interval (ms), and corrected QT interval (QTc, ms);(ix)Systolic and diastolic blood pressure (mmHg), measured on the left arm with participants seated in a quiet room after 5 minutes of rest, using an Omron digital sphygmomanometer;

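### The printed ELISA cut-off sits at the average of the negative controls with no margin, so any reactive/negative call would be invalid; separately, the primary serology variable is left as raw absorbance

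*Protocol article*

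**What the plan says.** The section on anti-T. cruzi antibody titers and antigen quantification describes a commercial recombinant ELISA, run "following the manufacturer’s recommendations". On controls it says: "Positive and negative controls will be included to ensure test functionality". It then gives the decision rule: "The cut-off value will be calculated as the mean absorbance of the negative controls". No SD, constant or multiplier is added to the average. The grey zone is placed around the same value: "with the indeterminate zone defined as within ±10% of the cut-off value".

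Item (iv) of the list of continuous variables describes the serology variable as "IgG antibody titers, quantified by ELISA and reported as absorbance values". It mentions no ratio to a cut-off or calibrator.

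The Study design section places serology in the primary outcome: "inflammatory profile, serologic reactivity to anti-*T. cruzi* antibody, and parasitic load". Table 1 lists antibody titers under the trypanocidal effect, measured once, at recruitment. Entry requires "Confirmed diagnosis of CD, based on two serological tests with different methodologies".

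**The concern.** There are two separate defects, and neither causes the other.

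1. **The cut-off.** A threshold that separates negative from reactive samples has to lie above the bulk of the negatives. This one lies at their centre, and its indeterminate zone surrounds typical negative samples instead of the boundary region. Anyone who applied the printed rule to report patients as reactive, indeterminate or negative would get calls with no diagnostic meaning. It is a stated formula for a primary-outcome assay, so it cannot be excused as detail left to a fuller document.

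2. **The scale.** In the same list, cytokines, nitrate/nitrite and parasite load have concentration units and gene expression is a fold change. Serology alone among these laboratory measures stays on the instrument's own scale. Each patient is measured once, so no within-patient change can cancel run effects. If more than one plate or run is used, differences between runs enter the comparison of exposed with non-exposed patients.

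**Working it through.** The article gives no error rate, assay CV or plate variance, so there is no figure to reproduce. The inputs from the document are a cut-off equal to the negative average, an indeterminate zone of 0.9 to 1.1 times the cut-off, and 45 patients per group (Sample size section). Everything else below is an assumption.

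**Cut-off.** Let true-negative absorbance be normal with mean μ and SD c·μ, where c is the CV, and set the cut-off at μ.

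- Above the cut-off: 1 − Φ(0) = 50%, whatever the CV.
- Called reactive (above 1.1μ): 1 − Φ(0.10/c).
- Indeterminate: 2Φ(0.10/c) − 1.
- Called negative: the same share as reactive, by symmetry.

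| Assumed CV | Reactive | Indeterminate | Negative |
|---|---|---|---|
| 5% | 2.3% | 95.4% | 2.3% |
| 10% | 15.9% | 68.3% | 15.9% |
| 15% | 25.2% | 49.5% | 25.2% |
| 20% | 30.9% | 38.3% | 30.9% |
| 50% | 42.1% | 15.9% | 42.1% |

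No CV rescues the rule: as fewer negatives fall in the indeterminate zone, more are called reactive. Simulating the average from 2 or 3 control wells raises reactive calls to 19.9–21.6% at CV 10% and 33.6–34.5% at CV 20%.

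To show what a margin does, take a cut-off of μ(1 + 2c), that is, mean + 2 SD. This is an illustration only, since the kit's formula is not in the document. The reactive share is 1 − Φ((1.1(1 + 2c) − 1)/c). At c = 0.10 this is 1 − Φ(3.2) = 0.07%, and it is at most 0.8% for CVs from 5% to 50%. The indeterminate share is 21.1% at CV 10% and 9.3% at CV 20%.

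**Does the cut-off reach the primary comparison?** Item (iv) is continuous absorbance. The Statistical analysis section compares continuous variables by t-test or Mann-Whitney test. The list of categorical variables contains no serological class. Changing the cut-off leaves every absorbance value, and so the group comparison, unchanged.

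**Raw absorbance.** Let r be the between-plate SD divided by the within-group SD. Treat plate variation as independent extra noise per sample, with samples placed without regard to group and plate ignored in the analysis. For an assumed 0.6 SD effect, power = Φ(0.6 / (√(1 + r²) · √(2/45)) − 1.96).

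- r = 0: Φ(2.846 − 1.96) = 81%
- r = 0.25: 79%
- r = 0.5: Φ(2.546 − 1.96) = 72%
- r = 1: 52%

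If instead each group were run on its own single plate, the group difference would carry an error with SD r√2: 0.35 within-group SDs at r = 0.25 and 0.71 at r = 0.5. On one plate for everyone, dividing by the cut-off rescales all values by one constant, so the ratio neither helps nor harms.

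**The case against.** The strongest reply is that the printed cut-off does no demonstrable harm. The stated measure does not use it, no endpoint is a reactive/negative class, all participants enter with confirmed disease, and serology is sampled once, so loss of reactivity during follow-up is not observed. The section already defers to the manufacturer, so the sentence may be an incomplete transcription of the kit's rule. On plates, the article gives no number, dates or layout. Serum is stored at −80 °C, which would permit a single batch, and layout is laboratory detail that an article may omit.

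Most of this stands. A reader might infer that the bad cut-off makes the primary serology endpoint invalid, or that the endpoint is not comparable across plates. The document supports neither: the first because the variable does not depend on the cut-off, the second because use of several plates is not stated. Nor do the true-negative percentages measure harm to the comparison of amiodarone users with non-users.

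What the reply does not remove is the formula itself. Whether chosen or mistranscribed, it cannot identify a negative sample, and it should not stand as the published rule for this assay. Nor is the use of absorbance an inference from silence, since the article states it.

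**Conclusion.** The point holds in two limited parts.

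- **Cut-off:** the printed rule is wrong as written. Half of true negatives exceed it for any symmetric distribution. The split between reactive and indeterminate depends on assumed CVs and normality, and matters only for categorical calls. The rule must be reconciled with the statement that the manufacturer's procedure is followed.
- **Scale:** raw absorbance exposes a primary-outcome variable to between-run variation if there is more than one plate or run. The loss could be small (81% to 79% power at r = 0.25) or material (72% at r = 0.5). Both r and the 0.6 SD effect are assumptions.

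Neither part shows that the planned comparison is biased.

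**What to change.** 1. Replace the cut-off sentence with the formula in the kit insert, and state the indeterminate zone relative to that cut-off.
2. In item (iv), define reactivity as the sample-to-cut-off ratio computed from each plate's own controls. Alternatively, keep absorbance and include a plate term in the group comparison if more than one plate is used.

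Optional: spread exposed and non-exposed samples evenly over plates, and call the variable a reactivity index instead of a titer.

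The cost is wording and a small analysis change. No additional assay or patient is needed. Values already read can be converted if the control readings for each plate were kept.
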